### Sample size calculation

Since this is an exploratory cohort study, no formal sample size calculation was done. Assuming 30 clinics to participate and a recruiting rate of about evaluable 30 patients per centre, we assume to have the data of about 900 patients to evaluate. This sample size is big enough to give answers with a good precision overall and in specific subgroups such as different cancer entities.

### Missing values

Due to the nature of the study (observational cohort study) no imputation of missing values will be provided. Appearance and frequency of missing data is examined in line with the objectives of the study.

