### Objectives

The primary aim of the study is to evaluate associations between the clinical outcomes and the two PROMs in the short-term (within 30 days) and long-term (after 3 and 6 months) in order to find out whether and to what extend complications (none/grade I vs. minor (grade II) vs. major (grade III-V)) influence the two PROMS in 5 predefined surgical cancer subgroups (upper-GI, pancreatic, hepatobiliary, colorectal, other abdominal cancers).

Further objectives are:To describe the absolute values of a.) the newly defined CAT EORTC QLQ-C30 and b.) the set of 12 cancer-specific symptoms [14] measured via the PRO-CTCAE [13] for oncologic patients undergoing surgery at predefined times from baseline (preoperative) until 6 months postoperative in the 5 surgical cancer subgroups outlined above.Although both of the proposed PROMs (PRO-CTCAE [13] and CAT version of the EORTC QLQ-C30) used in this trial have been validated, they are new and have never been tested head-to-head. Therefore, the existence of possible overlapping domains in both PROMs will be analysed.In order to find out if a student-led multicentre observational study using an electronic data capture system is feasible.

For the primary objective and further objective 1. and 2., the two PROMs (PRO-CTCAE and CAT version of the EORTC QLQ-C30) in the short-term (within 30 days) and long-term (after 3 and 6 months), as well as is the rate of postoperative complications grade II (minor) and III-V (major) within 30 days according to the Clavien-Dindo classification and the overall survival within 6 months postoperative will be assessed.

For further objective 3 the following endpoints will be assessed:Rate of missing PRO data at 3 and 6 monthsRate of missing clinical data at 30 daysNumber of participating trial sites including patients compared to initiated trial sitesRate of included patients in comparison to screened patients

Further endpoints can be found in the description of the study visits.

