### Statistical procedures

Since this is an exploratory study, all analyses will be descriptive and *p*-values < 0.05 will be referred to as statistically significant in descriptive sense. The patient characteristics and outcomes will be described for the whole cohort and for the different subgroups divided according to tumour entity with appropriate descriptive statistics (mean, standard deviation, median, interquartile range, minimum, maximum in case of continuous data and scores, or absolute and relative frequencies in case of categorical data).

To analyse the association between perioperative complications (Clavien-Dindo grading) and the set of 12 PRO-CTCAE symptoms as well as the subscales of CAT EORTC QLQ-C30 in the short- and long-term, Spearman’s rank-correlation coefficients (Spearman’s rho) will be calculated and analysis of variance will be performed.

For the description of the absolute values of the CAT EORTC QLQ-C30 as well as the set of 12 cancer-specific symptoms measured via the PRO-CTCAE appropriate descriptive measures will be reported.

Possible overlapping between the two PROMs (PRO-CTCAE and CAT EORTC QLQ-C30) will be analysed calculating Spearman’s rhos between the respective scales.

The rates of missing PRO data, clinical data and the rate of included patients compared to screened patients will be calculated and reported with adequate descriptive measures. The number of participating trial sites including patients compared to initiated trial sites and the rate of included patients in comparison to screened patients per trial site will be calculated, as well. The achievement of the respective goal rates will be evaluated by binomial tests.

Further analysis includes correlations between ASA score, comorbidities, neoadjuvant therapy, socio-economic factors, smoking, alcohol consumption and other baseline factors and subscales of the two PROMs and complications. Survival analysis includes Kaplan-Meier graphs and log-rank-tests between different tumour entities. Cox regression analysis will be performed to evaluate possible relationships between survival and different baseline covariates.

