## Discussion

Given the potential advantages of PROMs in clinical trials [8, 43] astonishingly little focus has been put on PROMs in surgical oncology. Here PROMs are frequently analysed inadequately (e.g. not addressing missing data) and are rarely the main focus of investigation. Consequently, very little is known about the relationship of clinical endpoints including postoperative surgical complications and PROMs in surgical oncology. In addition, previous studies investigating the relationship between PROMs and complications in abdominal cancer surgery have frequently used a cross-sectional design with inadequate validity [17–19] and results are thus questionable [20]. Moreover, most studies have focused on colorectal cancer surgery only, have reported conflicting results and lacked standardized complication measurements.

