Although PROMs have numerous potential advantages their true benefit has been limited and PROMs have ‘[…] rarely been informative from a licensure perspective’ [8]. The reasons for this are methodological aspects of PROMs that are frequently not adequately addressed in clinical trials including a.) inadequate PROM development [43]; b.) inadequate psychometric reliability, validity and responsiveness [43, 45]; c.) lack of an a priori specification of the expected effect size, PRO domain under investigation and sample size calculation [8] and d.) missing data, adding to attrition bias and necessitating the a priori specification of imputation methods [46]. While the first two aspects are not a concern for the two PROMs selected for our study, sample size calculation and missing data might be a concern, especially in surgical oncology with patients experiencing complications being less likely able to fill out PROMs. PATRONUS will create a sound database for sample size calculation for future clinical trials and will also offer a good estimate of the rate of missing data which can be expected in the context of surgical oncology and digital PROM assessment.

An important aspect of the PATRONUS study is the design and conduct by medical students. PATRONUS allows medical students to interact with concepts and methods of clinical research thereby potentially inspiring their orientation towards academic careers and work as clinician scientists [27, 28]. Although the conduct of multicentre clinical observational studies is relatively new, previous examples in the UK have shown the feasibility of this concept [33]. However, PATRONUS will add some important aspects compared to previous studies as patients will need to undergo written informed consent, PRO evaluation is performed, the follow-up is significantly longer and the study design more complex.

The limitations of the PATRONUS study are numerous. First, it is a single-arm observational study and therefore cannot elucidate a causal relationship. It will, however, serve to generate hypotheses for future clinical research.

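### The no-imputation rule rests the primary PROM contrast on responders only, against the protocol's own standard, and may bias it, most plausibly towards no effect

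*Protocol article*

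**What the plan says.** The Missing values section of the protocol article sets the rule and gives one reason for it: "Due to the nature of the study (observational cohort study) no imputation of missing values will be provided". The only other commitment there is descriptive: "Appearance and frequency of missing data is examined in line with the objectives of the study".

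For the primary association, Statistical procedures says that Spearman's rank correlations "will be calculated and analysis of variance will be performed". The exposure is set out under Objectives, which ask whether and how far "complications (none/grade I vs. minor (grade II) vs. major (grade III-V)) influence the two PROMS in 5 predefined surgical cancer subgroups".

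The Discussion takes a different position. Among the methodological weaknesses of PROM studies it lists "missing data, adding to attrition bias and necessitating the a priori specification of imputation methods". It then says missing data might be a concern for this study, "especially in surgical oncology with patients experiencing complications being less likely able to fill out PROMs". Earlier in the Discussion, failure to address missing data is the example given of inadequate PROM analysis in other surgical oncology studies.

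**The concern.** An observational design is no reason to leave missing outcomes unaddressed. Selective non-response distorts a comparison between exposure groups in a cohort just as it does in a trial. Without imputation, the two named methods become available-case analyses at each visit. The protocol itself expects response to depend on complications, which is the exposure being studied.

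The primary aim asks about the extent of the influence as well as its existence, so the size of the contrast is the result. The Discussion also wants the data to support sample size calculations for later trials, and a distorted difference would carry over into those.

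**Working it through.** **What the document supplies.** Its only planning figure is the number of evaluable patients: 30 centres × 30 patients = 900, which reproduces. It gives no effect size, SD, complication rate or missing rate by grade, so all inputs below except the 900 are assumptions.

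**Assumed inputs.** Grades none/I, II and III–V in 60/20/20% of patients; mean scores 60/55/50 (higher is better); SD 20. The intended difference, none/I minus III–V, is 10. In the simulated 1,000,000 patients it came out at 10.13, with rho −0.19. Missing rates by grade were 10/20/30%, 15/25/40% or 10/30/50%.

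**Formula.** Let z_k be the mean standardised deviation from the group mean among responders in group k. Then

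observed difference = true difference + SD × (z_none/I − z_major).

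The contrast is biased only if responders are selected more strongly on their score in one group than in the other.

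**Results by mechanism** (slopes are logits per SD of score)

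| Missingness depends on | Observed difference | rho |
|---|---|---|
| Grade only | 10.0 to 10.2 | −0.18 to −0.17 |
| Equal 20% in every grade, plus own poor score | 10.1 to 10.2 | about −0.20 |
| Grade plus own poor score, slope 0.5 | 8.3, 7.8, 6.4 | −0.15 to −0.11 |
| Grade plus own poor score, slope 1.0 | 6.9, 6.2, 3.7 | −0.13 to −0.07 |
| Grade plus own good score (15/25/40%) | 12.5 to 14.1 | −0.22 to −0.26 |
| Grade plus measured baseline (correlation 0.5, slope 1.0) | 8.5, 8.2, 6.9 | not computed |

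In the first row both z terms are zero. In the second they are equal and cancel. Attenuation needs two things together: worse-off patients missing within a group, and more missingness in the complication groups.

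**Size when an earlier measured score drives missingness.** From the last row: 1 − 8.52/10.13 = 16%, 1 − 8.16/10.13 = 19%, 1 − 6.87/10.13 = 32% too small. Adding baseline to the model gives 10.1 in all three cases.

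A second setting had a true difference of −0.50 SD, 20% major complications, a correlation of 0.6 between earlier and later scores, and slopes of 0.5 to 1.0:
- With 35% against 15% missing, responders give −0.46 to −0.41.
- With 45% against 20% missing, they give −0.38.
- The shortfall is 1 − 0.46/0.50 = 8% up to 1 − 0.38/0.50 = 24%. Using the earlier score recovers −0.50.
- The mild end depends on how missing rates are set within groups. Matching them exactly in each group gave −0.44 (12%) in place of −0.46.

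**Scale against precision at 900 patients.** The 95% half-width is 1.96 × 20 × √(1/n_none/I + 1/n_major).
- No missing data: n = 540 and 180, half-width 3.4.
- 10/20/30%: n = 486 and 126, half-width 3.9; bias 10.13 − 8.52 = 1.6.
- 10/30/50%: n = 486 and 90, half-width 4.5; bias 10.13 − 6.87 = 3.3.

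In these scenarios the bias is about 0.4 to 0.7 of the half-width in the whole cohort.

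**The case against.** The strongest reply is that the Discussion says only that response depends on complications. Group means are taken within complication grade, so this alone does not bias the ANOVA contrast. **That stands.** A reader might infer that the rule necessarily pulls the result towards no effect. The text does not support that, because it also takes selective loss of the worse-off patients within the complication groups. The phrase "patients experiencing complications being less likely able to fill out PROMs" makes such loss plausible without stating it. Loss of better-off patients would push the difference the other way.

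A reader might also infer that the distortion is greatest at 3 and 6 months. The article gives no missing rates by visit, and it allows those visits by telephone. Inability to answer because of a complication could equally peak early.

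The rule forbids imputation only. A likelihood-based mixed model would comply with it, and details are left to an SAP that is not shown. So the document does not prove that a complete-case analysis is final. Still, the article names no method beyond rho and ANOVA for this association, and its stated reason for the rule remains unsound.

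Finally, the study is exploratory, disclaims causality and makes the rate of missing PRO data at 3 and 6 months a feasibility endpoint. This lowers the stakes and discloses the problem. Describing missingness does not correct a contrast affected by it.

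The recovery of the true value in the working is also partly built in, since missingness was generated from the same score that the model used. It shows what a missing-at-random method can do when that assumption holds. It is no evidence that it holds here.

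**Conclusion.** The point holds in conditional form. The no-imputation rule has no valid rationale, it conflicts with the Discussion's own standard, and with the named methods it restricts the primary PROM comparisons to responders. The contrast may be biased, most plausibly towards no effect, if the worse-off patients in the complication groups are the ones who do not answer.

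Neither size nor timing can be derived from the document. Under the assumed inputs the shortfall was about 8 to 32% when missingness followed an earlier measured score. It was larger in some scenarios where missingness followed the unobserved score itself, a case that a missing-at-random method cannot be relied on to repair. Both settings took the effect, SD, correlation, slopes, grade distribution and missing rates as given. The first also took baseline to be unrelated to grade.

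Deaths are a separate matter. Grade V belongs to the major group, and those patients have no score after death. Imputation would not be a proper answer for them.

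**What to change.** Replace the no-imputation sentence under Missing values, and match it in the SAP before database closure:

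1. **Primary PROM analysis valid under missing at random.** Use either a likelihood-based repeated-measures mixed model with baseline and all scheduled scores and complication grade by visit, or multiple imputation from baseline and earlier scores, grade, ASA and centre. In the mixed model, treat baseline as one of the repeated responses, so that the target stays the difference by grade that the ANOVA addresses. Under multiple imputation, rho can be computed in each completed data set and combined.
2. **Deaths.** Do not impute or extrapolate scores after death. State that the contrast is among patients alive at each visit, and report deaths by grade beside it.
3. **One missing-not-at-random sensitivity analysis**, shifting the imputed scores of non-responders in the complication groups towards worse values over a stated range.
4. **Available-case rho and ANOVA** kept as a sensitivity analysis.

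The cost is modest extra analysis work, SAP wording and reliance on modelling assumptions. Baseline and repeated PROMs are already scheduled, so no new data are needed.

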## Discussion

Given the potential advantages of PROMs in clinical trials [8, 43] astonishingly little focus has been put on PROMs in surgical oncology. Here PROMs are frequently analysed inadequately (e.g. not addressing missing data) and are rarely the main focus of investigation. Consequently, very little is known about the relationship of clinical endpoints including postoperative surgical complications and PROMs in surgical oncology. In addition, previous studies investigating the relationship between PROMs and complications in abdominal cancer surgery have frequently used a cross-sectional design with inadequate validity [17–19] and results are thus questionable [20]. Moreover, most studies have focused on colorectal cancer surgery only, have reported conflicting results and lacked standardized complication measurements.

Similar to our planned PATRONUS study Bosma et al. have used a prospective observational design to analyse patients undergoing colorectal surgery and found an association between the severity of complications (measured via Clavien-Dindo) and HRQoL within the first 6 weeks, but not after 12 months [22]. However, this study had a single-centre design, used the short version of the WHO HRQoL assessment instrument [44], which covers no cancer-specific symptoms and is a generic, i.e. not cancer-specific HRQoL tool. In contrast, Di Cristofaro et al. reported no significant relationship between complications and global HRQoL (EORTC QLQ-C30, -CR29) in their prospective trial of 166 patients in 3 centres undergoing colorectal cancer surgery [21]. The randomised-controlled CLASSIC trial (laparoscopic vs. open resection for colorectal cancer) reported yet another result by prospectively analysing the HRQoL (generic EQ5D and cancer-specific EORTC QLQ-C30/CR38) in 614 randomised patients [23]. In contrast to the previous trials, significant long-term differences in QoL between patients with and without complications were found for Physical and Social Function, Role Functioning, and Body Image on EORTC QLQ-C30/QLQ-CR38 analysis and Mobility, Self-care, and Pain/Discomfort on EQ5D analysis. In line with these findings Anthony et al. reported an association with postoperative complications (no standardised evaluation) and postoperative HRQoL at 12 months using the Functional Assessment of Cancer Therapy (FACT-C) tool in 63 patients undergoing open colorectal cancer surgery [24]. For other types of abdominal cancer entities, results are even rarer including the study by Heerkens et al. who found no statistically significant and clinically relevant differences in HRQoL (using the EORTC QLQ-C30, -PAN26 and RAND26 questionnaire) between patients with severe compared to no/mild complications following pancreatic surgery in their single centre study [25] and Rutegard et al. who has analysed the Swedish national cancer registry for patients undergoing oesophagectomy for cancer and reported significantly impaired HRQoL (EORTC QLQ-C30 and -OES18) at 6 months in patients who had experienced technical surgical complications [26].

In summary, studies investigating the relationship between postoperative complications and PROMs are sparse and many studies exhibit severe methodological shortcomings. In addition, studies have used a multitude of different PROMs impeding direct comparison of results. In the meantime, clear recommendations exist for oncological trials to focus on two PROMs, namely HRQoL (either generic, cancer-specific or cancer-type specific) and cancer specific symptoms [8, 14]. For the latter the NCI has recently published recommendations which cancer-specific symptoms should be evaluated in all cancer patients (core set of 12 symptoms) [14], but has not specified the tools that should be applied to measure these symptoms. The EORTC QLQ-C30 has become one of the most widely used tools to measure cancer-specific HRQoL over the last decades [39] and recently a computerised adaptive version has been developed but not yet tested in surgical oncology. Similarly, the PRO-CTCAE symptoms score might be a fitting candidate to assess the proposed core set of cancer symptoms but again its evaluation in surgical oncology is pending. Therefore, a prospective multicentre study using an accepted complication measurement (Clavien-Dindo classification) and the two new PROMs as planned in our PATRONUS study seems urgently warranted.

Furthermore, a direct comparison of the two tools in overlapping domains (cancer-symptoms) is pending given their so far limited application in oncology. Again this issue will be studied in our study.

Although PROMs have numerous potential advantages their true benefit has been limited and PROMs have ‘[…] rarely been informative from a licensure perspective’ [8]. The reasons for this are methodological aspects of PROMs that are frequently not adequately addressed in clinical trials including a.) inadequate PROM development [43]; b.) inadequate psychometric reliability, validity and responsiveness [43, 45]; c.) lack of an a priori specification of the expected effect size, PRO domain under investigation and sample size calculation [8] and d.) missing data, adding to attrition bias and necessitating the a priori specification of imputation methods [46]. While the first two aspects are not a concern for the two PROMs selected for our study, sample size calculation and missing data might be a concern, especially in surgical oncology with patients experiencing complications being less likely able to fill out PROMs. PATRONUS will create a sound database for sample size calculation for future clinical trials and will also offer a good estimate of the rate of missing data which can be expected in the context of surgical oncology and digital PROM assessment.

An important aspect of the PATRONUS study is the design and conduct by medical students. PATRONUS allows medical students to interact with concepts and methods of clinical research thereby potentially inspiring their orientation towards academic careers and work as clinician scientists [27, 28]. Although the conduct of multicentre clinical observational studies is relatively new, previous examples in the UK have shown the feasibility of this concept [33]. However, PATRONUS will add some important aspects compared to previous studies as patients will need to undergo written informed consent, PRO evaluation is performed, the follow-up is significantly longer and the study design more complex.

The limitations of the PATRONUS study are numerous. First, it is a single-arm observational study and therefore cannot elucidate a causal relationship. It will, however, serve to generate hypotheses for future clinical research.

Second, data quality might be a concern. It is unclear if the assessment of postoperative complications performed by medical students is comparable to the assessment of trained doctors or study nurses. However, the SIGMA study group has implemented a number of measures to ensure high quality data assessment including a data validation plan (see methods section), centralized monitoring and training of participating study personnel in the SIGMA clinical trials curriculum prior to study initiation. Briefly, this curriculum includes a.) an obligatory e-learning session on the Clavien-Dindo classification; b.) lectures on the basics of evidence based medicine, levels of evidence, study types, statistical analysis plan, ethics, laws and regulatory obligations, Good Clinical Practice, and basics of data management; c.) workshops on acquiring informed consent from patients with actors and video-feedback, on how to improve patient recruitment, RedCap database training and bedside-teaching with Clavien-Dindo assessment. Within the PATRONUS study, only limited onsite monitoring will be done. An external monitor will check whether signed informed consent forms are available from all patients. However, no source data verification will be implemented. This is in contrast to the more enhanced data verification plans of other related study projects (e.g. EuroSurg Imagine trial) [47].

Third, as pointed out above the rate of SSIs according to CDC will be assessed as a secondary outcome parameter in our study. It is known from the analysis of RCTs, that there is an underreporting of SSIs if assessed as secondary endpoints compared to the assessment as primary endpoint [48]. Nonetheless, as SSI are among the most frequent postoperative complications assessment seems necessary both from an education and clinical perspective.

Fourth, as this is the first student-led study in Germany and of the CHIR-*Net* SIGMA group, feasibility and recruitment is unclear. Finally, many aspects of the concept of student-led clinical research warrant further evaluation.

